# Alternative alignment clinical study: study protocol for a prospective, randomised, controlled study of the outcomes and cost effectiveness of triathlon CR knee replacement system: traditional philosophy versus alternative alignment philosophy

**DOI:** 10.1186/s13018-025-06551-z

**Published:** 2025-12-05

## Abstract

**Background:**

Despite being one of the most successful orthopaedic operation, a number of patients remain dissatisfied after TKR surgery. There has been a recent move by some to change surgical philosophy to aim to replicate the alignment of the patient’s own original knee—known as kinematic or alternative alignment. The purpose of this study is identify if using the alternative alignment technique can lead to significantly improved outcomes when comparted to the traditional alignment technique.

**Methods:**

A single centre, randomised control trial, powered to recruit 126 patients (63 in each arm). The primary aim is to identify if the group undergoing TKR using the alternative alignment technique have a significantly improved functional outcome at 1 year when assessed by the minimal clinically important difference of at least 5 points in the Oxford knee score by comparison to the group using traditional alignment technique. Various other secondary outcomes are set out in the main text.

**Discussion:**

A study examining short-, medium- and longer-term outcomes of alternative alignment is needed to see if outcomes for patients can be improved. This study has the potential to be of great importance in contributing to this question. Limb alignment has focussed on the need to achieve the zero-degree goal of hip, knee and ankle alignment. To achieve real 3D more natural alignment, surgeons have to accept this goal may not be correct. There is a need to achieve pre-arthritic/pre-morbid alignment and to evaluate if this can unlock the potential for improved patient outcomes. A prospective, randomised study with multiple outcome measures can deliver a major contribution to the knowledge base of this subject and influence surgical practice with the aim of improving patient outcomes and satisfaction.

**Trial registration:**

The study was approved by the Wales Research Ethics Committee (IRAS project ID: 225871), and was registered with clinicaltrials.gov (Identifier NCT03196011).

**Supplementary Information:**

The online version contains supplementary material available at 10.1186/s13018-025-06551-z.

## Introduction

Despite being one of the most successful orthopaedic operation, a number of patients remain dissatisfied after TKR surgery. In a study of 253 patients, 1 year after TKR, Noble et al. [1] reported 11% of patients were neutral in their satisfaction after their surgery and 14% reported that they were either dissatisfied (3%) or very dissatisfied (11%). Reasons for this dissatisfaction are not always clear.

Various changes to surgical technique have tried to address this over the years. These include computer assisted navigation and patient specific knee replacement parts. However, whilst computer assisted orthopaedic surgery seems to improve accurate component positioning, the clinical significance of this remains to be proven [2].

More recently, attention has focussed on the alignment of the leg. Classic mechanical alignment in TKR is meant to co-align the prosthetic components to the mechanical axes of the femur and tibia and restore neutral overall limb alignment [3]. Traditionally, surgeons have believed that implant durability is maximized when postoperative limb alignment is corrected to 0° ± 3° relative to the mechanical axis [4]. When implanting the tibial component of a TKR, the surgeon will try and put the device perpendicular to the tibial mechanical axis. This is done to try and make sure the stresses on the new knee are equally placed on both the medial and lateral sides of the joint to try and prevent asymmetrical or accelerated wear on one side of the prosthesis. However, Bellemans et al. [5] examined 250 asymptomatic volunteers and identified that 32% of men and 17% of women have a varus deformity of the knee. Therefore, for many people, placement of the tibial component perpendicular to the floor may result in the alignment of the leg changing considerably, putting new strains on the soft tissues around the knee itself as well as altering the biomechanics of the adjacent ankle and hip joints with the potential to generate soft tissue strain in these areas also. It is possible that this alignment change is a major contributing factor to the dissatisfaction of some patients with TKR.

Concerns that a failure to achieve “correct” positioning of the TKR components may adversely affect the survivorship of the artificial joint may not be well founded. Bonner et al. [6] reported upon the survivorship 501 TKRs after 15 years of follow up. 396 implants were within 3° of the mechanical axis and 105 were not. Whilst this latter group may have been expected to have performed inferiorly, the results showed no statistically significant difference in the survivorship of the 2 groups when revision for aseptic loosening was used as the end point for the analysis. Similarly, Parratte et al. [4] reviewed 398 TKR cases in whom 292 had post-operative limb alignment within 0°–3° of the mechanical axis and 106 were outside of this. They concluded that a postoperative mechanical axis of 0° ± 3° did not improve the fifteen-year implant survival rate.

Surgeons are therefore now questioning the old philosophy of alignment [7]. There has been a move by some to change their surgical practice, and instead to try and put the knee replacement parts in place in a way that replicates the alignment of the patient’s own original knee. This is known as natural, kinematic or alternative alignment. Several studies have been undertaken that look at this alternative alignment, and importantly, they have not shown any loss of satisfaction with results of knee replacement, and indeed are showing some signs that in the short term, function of the knee may be better with the new technique [8, 9]. A meta-analysis by Migliorini et al. [10], which took 30 studies into account, found no statistically or clinically significant difference in PROMs and revision rate between mechanical and kinematic alignment.

Waterson et al. [8] reported one year follow up data in 71 patients undergoing TKR randomised to either kinematic (n = 36) or mechanical alignment (n = 35). Kinematically aligned TKRs were reported to have comparable short-term results to mechanically aligned ones with no significant differences in function one year post-operatively. Interestingly, in this work, there was a greater improvement in the mean American Knee Society Score (AKSS) in the kinematically aligned group at six weeks when compared with the mechanically aligned group (p = 0.05). The measurements of peak torque in the quadriceps were also significantly better in the kinematically aligned group at six weeks and three months (*p* = 0.003 and *p* = 0.02 respectively) by comparison to the mechanically aligned group.

Mizner et al. [9] reported deficits in quadriceps force of 30–40% in patients for up to a year after TKR by comparison to age matched subjects. They describe reduction of quadriceps muscle performance has been correlated with fall risk, walking speed, speed and quality of sit-to-stand transfers, and performance during stair climbing in individuals older than 60 years of age. Such functional deficits can impact significantly on quality of life and this functional reduction could be a contributory factor to the dissatisfaction with TKR reported by some patients. Bade et al. [11] identified similar reductions in quadriceps strength after TKR at 1 and 3 months post-op that took 6 months to recover to pre-operative levels. If Waterson’s work on kinematic versus mechanical alignment shows improvements in early quadriceps function, then it is important to see if this can be progressed further and translated into improved function and satisfaction after TKR.

Dossett et al. [12] reported the results of their work and evaluated an alternative alignment method (kinematic alignment with patient-specific cutting guides) compared to the alignment results with mechanical alignment with conventional instruments. In this work, the authors point out that because a mechanically aligned TKR strives to correct limb alignment to a straight line, the kinematics of the knee can be altered. Two of their secondary outcome measures showed results in favour of the kinematically aligned knee: the Oxford score (OKS) (0 is best and 48 worst) was 8 in the kinematically aligned group and 15 in the mechanically aligned group, a difference of 7 points, which was significant (*p* = 0.001). The range of knee flexion was 120° in the kinematically aligned group and 115° in the mechanically aligned group, a difference of 5°, which was significant (*p* = 0.043).

In the short term at least, it would appear that alternative or kinematic alignment of TKR components has the potential to deliver improvements in patient generated outcomes, quadriceps torque and flexibility of the knee which in theory could increase the number of patients satisfied with TKR.

A study examining short-, medium- and longer-term outcomes of alternative alignment, with a contemporary TKR design is needed to see if outcomes for patients can be improved. This study has the potential to be of great importance in contributing to this question. Limb alignment has focussed on the need to achieve the zero-degree goal of hip, knee and ankle alignment. To achieve real 3D more natural alignment, surgeons have to accept this goal may not be correct. There is a need to achieve pre-arthritic/pre-morbid alignment and to evaluate if this can unlock the potential for improved patient outcomes. A prospective, randomised study with multiple outcome measures can deliver a major contribution to the knowledge base of this subject and influence surgical practice with the aim of improving patient outcomes and satisfaction.

## Study aims and objectives

### Primary aim

To identify if the group undergoing TKR using the alternative alignment technique have a significantly improved functional outcome at 1 year when assessed by the minimal clinically important difference (MCID) of at least 5 points in the Oxford Knee Score (OKS) by comparison to the group using traditional alignment technique.

### Secondary aims

To identify if the use of the alternative alignment technique when performing TKR results in:A faster post-operative recovery assessed by length of stay (LOS) in hospitalImproved short term function when assessed by peak quadriceps muscle torque measured by myometerLower hospital costs as a result of reduced LOSFaster increase in hamstrings muscle mass/torque measured by myometerEnhanced improvement in patient outcome scores (Knee Osteo-arthritis Outcome Score (KOOS), Oxford Knee Score (OKS), EQ5D) at short-, mid- and long-term timeframesEnhanced improvement in the results of the Exeter Functional Lab protocolEnhanced activity assessment, as measured by the Exeter University Department of Sport Science using an accelerometer in a subset of the first 40 participantsEnhanced positioning of the implants, as assessed by a CT scan rotational profile assessmentEnhanced range of knee flexionAny difference in wear characteristics of the prosthesisAny significant differences in component positioningAny significant differences in limb alignmentAny significant changes in 5 gait parameters as measured by the Instride AccelerometerAny significant difference in the Self-Administered Patient Satisfaction Scale (SAPS)by comparison to the TKR performed with traditional instruments.

We will achieve these aims by:Enrolling 126 patients into this study over a period of 5 yearsCarrying out a prospective randomised study looking at the subject matter over a period of 11 years (5 years recruitment; 5 years follow up; 1 year data analysis and write upAnalysing patients’ functional status pre- and post-surgery using patient generated questionnaires and data from the Exeter functional labAnalysing patients’ post-operative radiological results from the plain X-rays to look at limb alignment, component position and wearAnalysing the TKR component position on the pre and post–operative CT scansCollecting length of stay data taken from the patient administration systemCollating all of the data from the study into a spread sheet for analysis by a professional statistician

## Methodology

### Study design

This is a prospective, single-centre, partially blinded, randomised controlled trial conducted at the Exeter Knee Reconstruction Unit (EKRU), Royal Devon and Exeter (RD + E) Hospital. A total of 126 patients undergoing primary total knee replacement (TKR) will be randomised (1:1) to receive implantation using either traditional mechanical alignment or an alternative alignment philosophy. Randomisation will be performed using a computer-generated sequence, with allocation concealed in sealed opaque envelopes.

Blinding will be maintained for the patient, all outcome assessors, radiologists, physiotherapists, and university staff analysing accelerometer data. Blinding of these individuals will be ensured by not revealing the treatment arm to the outcome assessors, radiologists, physiotherapists and data analysts; and keeping mention of treatment arm to the operation note alone. The operating surgeon cannot be blinded due to the nature of the intervention. Follow-up assessments will be conducted at 6 weeks, 3 months, 6 months, 1 year, 2 years, and 5 years post-operatively.

The primary outcome is functional improvement at 12 months measured using the Oxford Knee Score (OKS). Secondary outcomes include muscle strength, implant positioning, radiological alignment, activity levels, patient-reported outcomes (KOOS, EQ-5D, FKS, UCLA, SF-36), range of motion, prosthesis wear, and healthcare utilisation.

### Identifying potential study participants

Patients will be identified as potential participants in one of two ways. Firstly, by their surgeon when they are initially listed for TKR surgery at their out-patient consultation at the RD + E. The surgeon will outline the study, provide the patient with the study patient information leaflet and a copy of the study consent form and ask permission from the patient to allow one of the research team to contact them to discuss the study further. Alternatively, potential participants will be identified from the current surgical waiting list as suitable for inclusion. In this latter case, their surgeon will write to the patient requesting permission for one of the research team to contact them by telephone to discuss the study and to enquire if the patient would enrol. A patient information leaflet about the study will accompany this letter.

The patient will have an opportunity to provisionally agree or decline enrolment during this telephone call.

The below table (Table 1), shows the enrolment, intervention and assessment timings, in accordance with the SPIRIT reporting guidelines. [13]

**Table 1 Tab1:** Schedule of enrolment, intervention, and assessments

	Study period								
	Enrolment	Allocation	Surgery		Post-surgery				Close-out
TIMEPOINT**			0	6 weeks	3 months	6 months	1 year	2 years	5 years
ENROLMENT:									
Eligibility screen	X								
Informed consent	X								
Allocation		X							
INTERVENTION:									
Surgery			X						
ASSESSMENTS:									
CT	X			X					
X-rays	X			X					X
Questionnaires	X			X	X	X	X	X	X
Functional Assessments	X			X	X	X	X	X	X

The below figure (Fig. 1) shows a flow diagram of the participant timeline.

**Fig. 1 Fig1:**
[figure not shown]
Participant timeline

Inclusion criteria:Patients undergoing primary TKR at the RD + E HospitalPatients must have completed a consent form for the studyPatients must be prepared to comply with the pre- and post-operative investigations, rehabilitation, attendance schedule and questionnaire schedule of the studyPatient in whom any varus deformity present is < 20°The diagnosis is of tricompartmental osteoarthritis of the kneePatient has primary diagnosis of Non-Inflammatory Degenerative Joint Disease (NIDJD).Body Mass Index (BMI) < 40Aged ≥ 50 years at time of surgery

Exclusion criteria:Refusal to consent to the studyIf the knee for surgery has a fixed flexion deformity ≥ 15°- this will be assessed by a lateral “heel-hang” X-ray of the knee for surgeryIf the knee for surgery has a varus deformity ≥ 20°If the knee for surgery has a valgus deformity i.e. hip/knee/ankle alignment angle < 0°Pre-op Oxford Knee Score < 8Pre-op knee flexion ability < 90°Any patient whose post-operative recovery or ability to comply with the post-operative rehabilitation and assessment schedules is compromised by known existing other medical conditionsPregnancyPrisonersA patient known to have substance abuse or psychological disorders that could interfere with their ability to comply with the post-operative rehabilitation and assessment schedulesPatients unable to read or understand the patient information leaflet and consent formBMI ≥ 40Patient has an active or suspected latent infection in or about the affected knee joint at time of study device implantation.Patient has received any orthopaedic surgical intervention to the lower extremities within the past year or is expected to require any orthopaedic surgical intervention to the lower extremities, other than the TKR to be enrolled in this study, within the next year.Patient requires bilateral total knee replacements, or has a history of unsuccessful contralateral partial or total knee replacement.Patient has chronic heart failure (NYHA Stage ≥ 2)Patient has a neuromuscular or neurosensory deficiency, which limits the ability to evaluate the safety and efficacy of the device.Patient is diagnosed with a systemic disease (e.g. Lupus Erythematosus) or a metabolic disorder (e.g. Paget’s disease) leading to progressive bone deterioration.Patient is immunologically suppressed or receiving steroids in excess of normal physiological requirements (e.g. > 30 days).Patient requires revision surgery of a previously implanted total knee replacement or knee fusion to the affected joint.

### Sample size

126 patients (63 per arm). The sample size was determined using the primary outcome measure, OKS measured at 12-month follow-up, which has an MCID of 5 units [14]. To detect a between group mean difference of 5 units, with 90% power and significance threshold of 0.05, using a standard deviation in both groups of 7.6, requires 50 participants per group. Thus, accounting for drop-outs, we aimed to recruit an additional 13 patients to each arm, bringing the total to 126 patients. For a completed SPIRIT checklist, see the additional file. [13]

### Obtaining participant consent/collection of pre-operative data

If the potential participants have given verbal agreement to enrol in the study, we will obtain written consent of participation when they attend the hospital for the pre-operative CT scan. The patient will meet one of the research team before the CT scan appointment in the out-patient orthopaedic appointment area to sign a study specific Ethics Committee approved study consent form. They will also complete the pre-operative data will be collected including: demographics and medical history, KOOS, OKS, the EQ5D score, the Forgotten Knee Score and the SF36, the UCLA activity score, pain measurements by Visual Analogue Scale (VAS) during rest and activity and detail of the use of pain medication. The research team member will perform an assessment of the participants overall joint flexibility using the Beighton scale. An assessment of pre-operative anxiety and depression will be made via the Hospital Anxiety and Depression Scale.

On the study consent form, we will ask for the participant’s agreement to contact their GP to inform them of inclusion in the study.

We will ask for specific patient consent to send personable identifiable information (patient name, date of birth and hospital number) as well as CT scan and X-ray images to LifeIMAGE in the United States (who act as a pass-through server to the Stryker segmentation team). We will also ask for the same permission for the scans to be passed to Stryker US via LifeIMAGE for the purpose of unique operation detail planning.

LifeIMAGE and Stryker US are the only companies able to provide the individually tailored surgical plan from the CT and X-ray data for use with the MAKO system.

3 copies of written consent will be obtained- one original and 2 photocopies. The original will be kept by the research team in the patient’s case record file (CRF), one will be returned to the patient and one will be placed in the medical notes.

Routine care for these patients from their clinic appointment will have already included X-ray of the affected knee, full leg alignment X-ray, and an assessment of their active and passive range of motion of the knee.

All information collected pre-operatively will be used to quantify the sample population and compare post-operative progression.

### Randomisation

This will be a randomised, prospective, blinded study with 2 arms of 63 patients each. The first arm will receive a Triathlon knee replacement device which is implanted using the traditional alignment philosophy in which the tibial cut is made perpendicular to the tibial anatomical axis. The second arm will receive a Triathlon TKR using the alternative alignment philosophy which aims to replicate the natural alignment of the knee.

Patients who agree to enter the trial will be divided at random to enter the different treatment arms of the study. The randomisation schedule will be determined using an on-line random assignment sequence generator (www.graphpad.com/quickcalcs/randomize1.cfm) and will be kept and controlled by the study co-ordinator, and the surgeons will not have access to this schedule. 126 patients will be included. Their randomisation assignment will be transcribed onto paper, and placed inside a sealed opaque envelope. The study co-ordinator or research nurse will inform the operating surgeon of the assignment of each patient at the weekly surgical planning meeting.

Any deviation from the assigned treatment group by a surgeon will be reported as a deviation from protocol and the case will be terminated from the study.

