## Statistical analysis

Independent statistical analysis of the results will be undertaken by an experienced statistician from the R + D department within our hospital.

All outcomes will be reported descriptively by group, with continuous outcomes reported as mean (standard deviation) or median (interquartile range).

All continuous outcome measures, including the primary outcome (OKS) will be analysed using linear regression modelling with adjustment for randomisation variables (surgeon, severity based on baseline OKS, and age (below 70, 70 and above), and baseline measurement). EQ5D will be analysed using the equivalent analyses with Tobit regression. Between group comparisons will be reported using confidence intervals and p-values.

For continuous measures recorded at multiple time points, hierarchical regression models will be used to assess the interaction between intervention and timepoint, with the interaction effect reported as a global p-value.

All analyses will be reported using the intention to treat principle. The primary analyses will include complete case data only. The amount of missing data will be reported for all outcome variables. In the event of substantive missing data (more than 5%), a secondary analysis will be performed including observed data and missing data imputed using multiple chained equations.

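### Terminating patients whose surgeon departs from the assigned alignment contradicts the intention-to-treat analysis and removes randomised patients on an unblinded decision

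*Protocol article*

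**What the plan says.** Under Randomisation, the protocol article sets a rule for patients not operated on as allocated. When a surgeon departs from the allocation, this is to be "reported as a deviation from protocol and the case will be terminated from the study". The same section has the study co-ordinator or research nurse tell the surgeon the allocation before the operation; they "will inform the operating surgeon of the assignment of each patient at the weekly surgical planning meeting". Study design adds: "The operating surgeon cannot be blinded due to the nature of the intervention".

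Under Statistical analysis: "All analyses will be reported using the intention to treat principle". Two further sentences there matter. The first is "The primary analyses will include complete case data only". The second brings in imputation only as an addition: "In the event of substantive missing data (more than 5%), a secondary analysis will be performed".

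The endpoint at stake is the primary one: "The primary outcome is functional improvement at 12 months measured using the Oxford Knee Score (OKS"). No section says that a terminated case is still followed up or kept in the analysis.

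**The concern.** Intention to treat compares the groups as randomised, whatever operation was done. A patient allocated to one alignment and operated on with the other is the kind of patient the principle exists to retain. The Randomisation section removes that patient.

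The removal happens after randomisation and follows from an act of someone who knows the allocation. A surgeon may depart from the allocated alignment because the knee is difficult or the plan looks unacceptable, and such reasons may be commoner under one alignment than the other. Concealed envelopes protect the assignment itself. They do nothing about who is removed afterwards. If removals differ between arms in number or in prognosis, the remaining patients no longer form a randomised comparison, and an analysis that excludes treatment departures would be reported under an intention-to-treat label.

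**Working it through.** **1. Following one patient through the text.** A patient is randomised. The surgeon learns the arm at the planning meeting and operates with the other alignment. Under Randomisation, the case is terminated. Read literally, follow-up stops at or soon after surgery and the trial holds no 12-month OKS. Under Statistical analysis, the primary analysis uses complete cases, so the patient is absent from it. The multiple imputation analysis is secondary and applies only above 5% missing. Since 6/126 = 4.8% and 7/126 = 5.6%, up to six patients could be lost in this way, with no other missing data, before it is triggered.

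**2. The plan's own sample size.** Inputs from Sample size: difference 5, SD 7.6, power 90%, significance level 0.05, 50 evaluable and 63 recruited per arm.
- Two-sided two-sample t-test: n = 49.5, rounded up to 50 per arm. This reproduces; power at 50 is 90.3%.
- Allowance for drop-out: 63 − 50 = 13 per arm, and 13/63 = 20.6%.

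The sample size is not in dispute.

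**3. Bias, on assumed deviation rates.** Suppose k of the 63 patients in an arm are terminated and their mean OKS would have been d points below that of the others, whose mean is m. The true arm mean is m − (k/63)d and the retained patients give m, so

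bias in the arm mean = (k/63) × d.

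This equals the bias in the treatment difference when only one arm loses patients. The article states neither k nor d; both are assumptions.

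| k | d | Bias (OKS points) | Share of 5-point MCID |
|---|---|---|---|
| 3 | 5 | 3/63 × 5 = 0.24 | 5% |
| 6 | 5 | 6/63 × 5 = 0.48 | 10% |
| 6 | 10 | 6/63 × 10 = 0.95 | 19% |
| 9 | 10 | 9/63 × 10 = 1.43 | 29% |

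**4. Effect on the false-positive rate.** Take k = 6 and d = 10 in one arm, no true difference and no other drop-out, with an unadjusted comparison by the normal approximation. The standard error is 7.6 × √(1/63 + 1/57) = 1.39, and bias/SE = 0.95/1.39 = 0.69. The two-sided error is P(Z > 1.96 − 0.69) + P(Z < −1.96 − 0.69), which is about 10.5% against the nominal 5%. With k = 3 and d = 5 it is about 5.3%.

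**5. Power.** How terminations affect power depends on the other losses (difference 5, SD 7.6, two-sided t-test):
- 6 terminated per arm and no other loss: 57 per arm, power 94%.
- Terminations and other losses together within the allowance of 13: at least 50 per arm, power at least 90%.
- 6 terminated per arm on top of 13 other losses: 44 per arm, power 86.2%.

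**The case against.** The strongest reply is that the article does not define termination. It may mean the end of trial procedures only. Post-operative follow-up says that the 1-, 2- and 5-year reviews are usually done by postal questionnaire, so some contact at one year exists outside the trial. A missing score might therefore be recoverable, and it would be too strong to call the loss irreparable. That stands. But the article does not say that the OKS is part of that questionnaire, and no section says that follow-up of terminated cases continues. Staff who follow the text would stop it.

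A second reply is that the size is hypothetical. This also stands. Six or nine of 63 means 10% to 14% of an arm, and d = 10 is 1.3 times the assumed SD. Similar losses in both arms would largely cancel, and adjustment for baseline OKS, surgeon and age would remove part of any prognostic imbalance. Eligibility limits on deformity, CT-based planning with a separate algorithm for each arm, experienced surgeons and three-monthly review of deviations all make crossover less likely. The power loss is modest, and there is none below 90% while total losses stay within the allowance.

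Third, the rule may be meant as a deterrent, and it gives surgeons no stated right to remove patients. That is a fair reading of its purpose. Its effect is unchanged: the surgeon's departure is what triggers removal.

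None of this reconciles the two sections. Nor is it a detail left to a fuller document, because both statements are in this article and one orders what the other rules out.

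**Conclusion.** The concern holds and should be fixed. The contradiction rests on the text alone and needs no assumption about deviation rates: a patient terminated for receiving the other alignment cannot also be analysed as randomised from data the trial has stopped collecting. If no surgeon ever deviates, no harm results. If some do, the primary comparison loses patients for a reason that may be linked to arm and outcome.

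The main risk is bias. It runs from 0.24 to 1.43 OKS points under the assumed range, if removals fall in one arm and the removed patients would have scored 5 to 10 points lower, before any gain from covariate adjustment. Loss of power is secondary: 86% in the least favourable case shown.

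**What to change.** Replace the sentence under Randomisation with wording such as: *Any departure from the assigned alignment will be recorded as a protocol deviation. The patient stays in the study, completes all scheduled follow-up and is analysed in the arm assigned.* Put any exclusion of deviating cases into a per-protocol or as-treated sensitivity analysis, and report the number of deviations by arm with reasons. For any case already terminated, obtain the 12-month OKS where consent allows.

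The cost is a one-sentence amendment and continued follow-up of what should be a few patients, who have already agreed to the visit and questionnaire schedule as a condition of entry. Crossovers may slightly dilute the estimated difference, which is the accepted consequence of the principle the plan has already chosen. The change concerns retention and analysis only and takes no position on when a surgeon may depart from the allocated alignment.
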